## Discussion

It is not uncommon for an initial native biopsy on a patient with steroid resistant nephrotic syndrome to show MCD, only to have subsequent biopsies for disease progression demonstrate FSGS. One series of 77 transplants for FSGS showed that 13% had MCD on an initial native biopsy with FSGS on a subsequent biopsy (30). Recurrent disease was equally likely to occur with MCD or FSGS on initial biopsy, therefore we have included both in this trial.

One limitation of this trial is that genetic testing is not required to exclude those with genetic causes of nephrotic syndrome that would be unlikely to recur. Pediatric centers routinely perform genetic testing for all patients with FSGS and those with genetic cause would be excluded for this trial, however this is not the case for all adult transplant centers and is currently not recommended by KDIGO guidelines. Similarly, enrollment in this study requires the judgement of the clinical investigator to exclude patients with typical secondary causes of FSGS. The inclusion and exclusion criteria are consistent with the field’s current standard for evaluation of FSGS and aim to enrich the study population with those who are more likely to have recurrent disease. An additional potential limitation of this study is that the power calculation was performed using data from a pediatric population given lack of consistent data in the adult FSGS population during the study design phase. Since study initiation, a large multicenter review described a recurrence rate in adults with primary FSGS to be 37% in a US population, slightly lower than 42% recurrence rate in pediatric patients which may lead to an underpowered study (31).

Several participating centers were offering preemptive plasmapheresis to patients at high risk of recurrent FSGS prior to the initiation of this trial. We chose to add Rituximab to this baseline given the complexity of requiring a center to remove a therapy they were already offering. This trial was designed to include a single episode of pheresis with a single dose of rituximab prior to transplant as a pragmatic decision to allow for therapy to be completed during the short window prior to deceased donor kidney transplantation. Future studies would be required to evaluate whether there is a potential benefit from additional pre-transplant doses of rituximab and to determine the optimal number of plasmapheresis sessions, if any.

The purpose of this study is to test the effectiveness of rituximab in combination with plasmapheresis prior to kidney transplant, in reducing the incidence of recurrent FSGS after kidney transplantation. In recipients in whom FSGS does recur, we will study the impact of these interventions on the time to FSGS recurrence. In addition, we will be monitoring transplant outcomes (graft survival rate, rejection rate and estimated GFR at 1 year post-transplant) and patient outcomes (patient survival at one year post-transplant). The safety of plasmapheresis and rituximab will be assessed. Since studies in nephrotic syndrome have demonstrated that the rituximab effect is lost with recovery of the CD19+ cell population (32), we will study the proportion of patients with CD19^+^ <1% at 1 month, 6 months, and 12 months in the rituximab arm of the study. Single center studies have had conflicting results on the effectiveness of preemptive plasmapheresis on rate of recurrence of FSGS; however a recent meta-analysis did not demonstrate benefit of plasmapheresis alone (33). Similarly, single-center primarily retrospective studies of rituximab for prevention of recurrent FSGS have had mixed results with some suggesting benefit (24, 26, 33). We have designed a first of its kind randomized controlled multicenter study in adult and pediatric kidney transplant candidates with primary FSGS as the cause of end-stage kidney disease.

### Study progress to date

The success of this study depends on recruitment and adherence to the randomization protocol. Recruitment in previous clinical trials of FSGS was impeded by stringent definitions of primary FSGS, an overestimation of anticipated case number at each site, and lack of site investigator enthusiasm for the study intervention (34, 35). To mitigate these issues, we allowed site investigators to use their discretion to determine if a patient had primary or secondary FSGS and utilized SRTR 3-year data on ESKD etiology for case number prediction at each site.

Due to the COVID-19 pandemic, most transplant centers in our study had inactivated their transplant programs for varying periods of time. Responsively, we halted recruitment in March 2020 and reopened in June 2020, although the extent and timing of study closure varied by site. One of our centers subsequently withdrew from participation due to lack of research personnel for non-COVID-19 study purposes. One of our study sites withdrew from the study due to center rules which precluded research coordinators from coming to the hospital for non-COVID-19 studies.

Given the delays in study recruitment due to the COVID-19 restrictions, a number of changes to the initial inclusion criteria were made to allow for more rapid recruitment. The initial inclusion criteria were restricted to children and adults age ≤ 40 years to avoid the inadvertent inclusion of secondary FSGS which would confound results. Our study site investigators in adult programs were concerned that eligible patients would be eliminated with such stringent inclusion age criteria and so these were expanded to include those under 65 years of age starting in July 2021. Similarly, the initial protocol allowed inclusion of transplant recipients at the time of their first or second transplant. After feedback from sites and coordinators, this criteria was expanded to include patients receiving their third transplant as well in July 2021.

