A number of clinical risk factors for recurrent FSGS have been identified including prior recurrence, European ancestry, rapid progression of primary FSGS to ESKD within 3 years, mesangial hypercellularity on primary biopsy and living related donor transplant; however these findings are inconsistent among various small studies (2, 5). A recent study from Europe identified late steroid-resistant FSGS (nephrotic syndrome that becomes resistant to steroids after an initial therapeutic response) as a strong risk factor for recurrence (3). These findings have been replicated in our recent retrospective study of a North American cohort from the Pediatric Nephrology Research Consortium (N=116) that showed that the risk of recurrent FSGS was 71% in children with late steroid-resistant FSGS compared to 36% in children with initial steroid-resistant FSGS (6). Genetic risk factors for late steroid-resistant FSGS are unknown. In the same study, we identified native kidney biopsy findings that may predict risk of recurrence. Unfortunately, an individual’s risk of recurrent disease cannot be predicted accurately prior to transplant. Thus, patients with FSGS have a high risk of recurrent disease post-transplant that is difficult to predict and leads to poor outcomes.

Post-recurrence treatment with plasmapheresis or rituximab, although often utilized, is not effective in all patients. Effective therapies and prevention strategies for recurrent FSGS are lacking (7–10). The demonstration of a possible causative circulating factor by Savin et al. (11) galvanized the field to attempt plasmapheresis to remove the permeability factor as a therapy for recurrent FSGS. Thereafter, recurrent FSGS has most often been treated with plasmapheresis to remove the as yet undetermined circulating factor, which is effective in a subset of patients. The results of uncontrolled single center case reports and series suggest a benefit from plasmapheresis (12–14), although graft loss from recurrent disease remains unacceptably high. Others who do not respond to plasmapheresis have been treated with alternate agents such as rituximab, abatacept, or high dose cyclosporine with variable responses and are at risk for rapid progression to graft failure (15–17). Ideally, we need to identify strategies to prevent recurrent FSGS before it occurs, which will lead to longer kidney transplant survival and reduced health care costs.

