### Sample size

Our recent retrospective study from the Pediatric Nephrology Research Consortium demonstrated an overall recurrence rate of 43% in children with FSGS, including patients both with and without monogenic cause of disease (35.8% in patients with initial steroid-resistant FSGS vs. 70.6% in patients with late steroid-resistant FSGS) (6). Sample size estimates are based on 80% power to detect the described difference as statistically significant at a significance level of 0.05. Seventy subjects per group (140 in total) are required to detect as significant a decrease in the rate of recurrent disease from 43% in the control group to 21% in the treatment group (50% reduction). We will target enrollment of 160 patients to account for ~15% attrition or loss to follow up.

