### Statistical plan and data analysis

Demographic and baseline characteristics of study participants will be summarized using descriptive statistics and compared between treatment groups using two-sample t test for continuous variables and Chi-square test for categorical variables.

The proportion of patients with recurrent disease at 1-year post-transplant (the primary outcome) will be compared between treatment groups using Chi-square test. Multivariate logistic regression model will be constructed to model the probability of recurrence. The model will include treatment group, center, and covariates determined by the investigators to impact recurrent and/or those that are significantly different between groups at baseline. Binary secondary outcomes (graft survival, patient survival, acute rejection, and CD19^+^ <1%) will be analyzed similarly. Survival analysis will be performed to evaluate the effect of treatment on time to FSGS recurrence. Estimated GFR, a continuous secondary outcome, will be compared between groups using two-sample t test. Multivariate linear regression analysis will be conducted to examine the effect of treatment on eGFR adjusting for covariates.

Intention-to-treat analysis will be used. Analysis will be performed using Statistical Analysis Software (version 9.3, SAS Institute Inc., Cary, NC). A two-sided p-value < 0.05 will denote statistical significance.

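### The primary chi-square ignores the randomisation strata and prior graft recurrence, and further covariates may be picked by baseline significance: precision is forgone, although the planned power and error rate stand

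*Protocol article*

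**What the plan says.** Eligibility (Study population) covers first, second and third kidney transplants. Study progress to date explains that first and second transplants were allowed initially and that "this criteria was expanded to include patients receiving their third transplant as well in July 2021".

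On prognosis, the Introduction states: "A number of clinical risk factors for recurrent FSGS have been identified including prior recurrence". The same sentence goes on to list other factors and warns that the findings are inconsistent across small studies. Later the Introduction describes four patients with earlier graft loss from recurrence as being at very high risk, without giving a rate.

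Randomization and study treatment stratifies by initial versus late steroid resistance and by age under 18 versus 18 and over. Transplant number and prior recurrence are not strata.

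Under Statistical plan and data analysis, the primary proportion "will be compared between treatment groups using Chi-square test". A logistic model follows. It contains treatment group, center and "covariates determined by the investigators to impact recurrent and/or those that are significantly different between groups at baseline". Neither the two strata nor prior recurrence is named there.

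**The concern.** Three features combine.

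- The test that decides the trial uses none of the prognostic information the trial holds, including the factors it stratified on because their risks differ.
- A factor the authors themselves name, and which re-transplant eligibility makes relevant, is left to chance balance.
- The rule for adding covariates is poor. How much a covariate matters depends on how strongly it predicts recurrence, not on whether its baseline difference reaches p < 0.05. In an open-label trial, leaving the rest to investigator judgement also permits choices made after outcomes are visible.

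At stake is precision in a trial of about 70 evaluable patients per arm. The Discussion itself says that a lower adult recurrence rate may leave the study underpowered. A single chance imbalance could also cloud the result, with no pre-specified analysis to settle it.

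**Working it through.** **1. The plan's own figure.** Inputs from Sample size: "a decrease in the rate of recurrent disease from 43% in the control group to 21% in the treatment group", 80% power and significance level 0.05. Two-sidedness comes from the analysis section. With pooled variance and no continuity correction:

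n = [1.960·√(2·0.32·0.68) + 0.842·√(0.43·0.57 + 0.21·0.79)]² / 0.22² = (1.293 + 0.540)² / 0.0484 ≈ 69.4, so 70 per group.

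Power at 70 is 80.4%. The stated size reproduces, and it belongs to the unadjusted comparison.

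**2. What the baseline-significance rule lets through.** Take 14 of 70 against 7 of 70 with a prognostic factor, a 10-point imbalance. The pooled share is 21/140 = 0.15, SE = √(0.15·0.85·2/70) = 0.060, z = 0.10/0.060 = 1.66, p ≈ 0.10. The rule would not select this factor.

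**3. How often such an imbalance arises.** The share with prior recurrence is not in the document, so it is varied. With 140 patients split 70/70 and K carriers, the number in one arm is hypergeometric:

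| Assumed share (K) | SD of between-arm difference | Chance of 10 points or more, either direction |
|---|---|---|
| 5% (7) | 3.7 points | 1% |
| 10% (14) | 5.1 points | 5% |
| 20% (28) | 6.8 points | 14% |
| 30% (42) | 7.8 points | 20% |

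**4. What a 10-point imbalance does.** Let s be the share and r the control risk in carriers. The risk in the others is (0.43 − s·r)/(1 − s), and the shift in the crude difference is 0.10 times the risk gap.

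- s = 10%, r = 60%: others 41.1%, gap 18.9 points, shift 1.9 points.
- s = 30%, r = 80%: others 27.1%, gap 52.9 points, shift 5.3 points.

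So the shift is about 2-5 points against a planned 22.

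**5. Power forgone.** Simulation with 70 per arm and 40,000 trials per scenario. Marginal rates are held at 43% and 21%, the odds ratio is constant across factor levels, and the factor is left to chance balance. The unadjusted chi-square has about 81% power throughout. A Mantel-Haenszel test stratified on the factor gives:

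| Assumed share | r = 60% | r = 70% | r = 80% | Gain over chi-square |
|---|---|---|---|---|
| 5% | 80.6% | 80.7% | 81.5% | about 0-1 points |
| 10% | 80.8% | 81.9% | 83.2% | about 0-2 points |
| 20% | 81.5% | 83.3% | 86.3% | about 0-5 points |
| 30% | 82.0% | 85.2% | 89.6% | about 1-9 points |

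Type I error is 4.7-5.3% for both tests.

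**6. The same check on a stratum, using the document's own rates.** Sample size gives 35.8% recurrence in initial and 70.6% in late steroid resistance, 43% overall. The implied late share is (43 − 35.8)/(70.6 − 35.8) = 20.7%. Stratifying the test on that factor alone raises simulated power from 81.0% to 83.5%. This run also left the factor to chance balance, whereas the trial stratifies on it, so it is only a guide to the size of the gain.

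**The case against.** The unadjusted chi-square is valid and the trial was sized for it. Chance imbalance is ordinary random error that the test already allows for. The authors call prior recurrence a risk factor, so it fits the investigator-judgement clause of the logistic model, and a full covariate list is commonly left to an analysis plan, which is not shown. The factor for which the document gives contrasting rates, steroid-resistance type, is a stratum. All this stands, except that a later plan would have to override the baseline-significance rule, which is stated here and not merely left open.

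A reader might infer more than the documents support:

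- **That the trial loses planned power.** It does not. The 80% was computed for the unadjusted test. What is missing is a possible gain.
- **That false positives are inflated.** Suppose 15% have prior recurrence at 80% risk, and controls happen to have exactly 10 points more of them. The one-sided false-positive rate is then about 6% rather than 2.5%. That is conditional on one adverse imbalance. The opposite imbalance is equally likely, and over all randomisations the rate stays at about 5% two-sided.
- **That the risk after prior recurrence is 80%.** The Introduction gives 80% as the top rate in an unspecified subset and does not tie it to prior recurrence.
- **That prior recurrence is the strongest factor because it is listed first.** The list is not a ranking, and it carries the inconsistency caveat.
- **That the July 2021 change created the issue.** Second transplants were eligible throughout; the change only widened it.

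**Conclusion.** The point holds as a cheap improvement, not as an error in the design. The primary analysis ignores the randomisation strata and a named risk factor, and the covariate rule can pass over a sizeable imbalance such as 14 versus 7. The planned power and type I error are sound.

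The size of the gain rests on two unknowns: the share of participants with prior recurrence and their recurrence risk. It is negligible if few participants qualify. It becomes material only at shares of about 20-30% with risks of about 70-80%. The case for adjusting for the strata and for dropping the significance rule does not depend on those unknowns.

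**What to change.** Leave randomisation as it is. In Statistical plan and data analysis:

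1. Make the primary comparison a stratified test, or a logistic model reported as a standardised risk difference. Pre-specify steroid-resistance type, age group and prior graft recurrence (yes versus no or first transplant). The standardised difference stays on the scale of the planned 22 points. Three binary factors give at most eight cells, and a Mantel-Haenszel test tolerates sparse ones.
2. Keep the unadjusted chi-square as a supportive analysis.
3. Delete covariate selection by baseline significance, and list any further covariates before outcome data are examined.

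If the unseen analysis plan already does this, the two texts need only be aligned.

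The cost is wording and slightly more analysis work, with little return if few patients have prior recurrence. One item must be confirmed: Table 1 lists medical history at screening but does not say that recurrence in earlier grafts is recorded. If it is not, it would have to be collected from existing records.
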